### Rescue analgesia

2.13

Patients who require an additional analgesic after PCA removal will be provided with tramadol 50 mg intramuscularly route each time. Usually, the need for supplementary treatment with systemic opioids is a reliable indicator when concerned about postoperative pain control. Having considered that the use of strong or long-term rescue analgesia in both groups may reduce pain too much and “washed out” any differences between the 2 groups. In this study, we use tramadol hydrochloride injection for rescue analgesia, which is a mid-intensity opioid analgesic that will facilitate observing the differences in pain control between groups. The frequency and total dosage during the first 3 postoperative days will be recorded.

### Outcome assessments

2.14

#### Data capture

2.14.1

Schedule for data collection is shown in Table 1. Specifically, the following data will be collected – demographic information, daily visual analog scale (VAS) pain score, sufentanil consumption, time to first use of IV-PCA, postoperative nausea and vomiting, rescue analgesia consumption, all other side effects and complications.

**Table 1 T1:**
[figure not shown]
Data collection schedule.

The VAS has been used extensively for rating pain intensity in previous studies.^[15–17]^ Postoperative pain at 6, 12, 24, 36, 48, and 72 hours after surgery will be recorded using the VAS pain scores. The VAS consists of a 10-cm horizontal line with 1-cm vertical lines at each end on which a score of 0 indicates no pain and a score of 10 indicates the worst conceivable pain. All data are verified against original documents by individuals who are independent of the trial.

### Primary outcome measures

2.15

The primary outcome was the average pain score over the incision site from the time of surgery up to 3 postoperative days after surgery

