### Sample size

2.17

The sample size calculation was based on the following parameters:

(1)alpha value = 0.05, 2-sided;(2)power = 80%.

The minimal clinical significance in VAS pain score was defined as the mean difference between current and preceding scores when the subject reported “a little worse” or “a little better” pain. Our pilot study shows that VAS pain scores 72 hours after lumbar spinal fusion surgery were reported to be 2.1 ± 1.6 in patients receiving cocktail analgesic injection and 5.6 ± 1.7 in patients without. Based on these findings, we hypothesized that VAS pain score 72 hours after surgery will be 2.5 for the cocktail group and 5.0 for the control group, with a standard deviation set at 2.5 and a ratio of patients in the cocktail to the control group of 1:1. Calculations showed that a sample size of 14 patients per group to detect a difference in VAS pain score between the 2 groups after treatment. Assuming a 20% dropout rate, 18 patients per group, or a total of 36 patients, are required.

It is anticipated that recruitment for this study will take 6 months to complete, using 1 surgeon to reduce surgical variability. Data collection for each patient will occur during the first 72 hours postoperatively and at a routine 4-week follow-up appointment. No further follow up will be routinely arranged. Any patients requiring specific follow up will have this arranged on an individual basis.

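### The primary outcome is the 3-day average pain score, but the sample size rests on the 72-hour score alone, so the stated 80% power is not shown for the primary endpoint

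*Protocol article*

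**What the plan says.** Section 2.15 names one primary outcome: "The primary outcome was the average pain score over the incision site from the time of surgery up to 3 postoperative days after surgery". The readings that can feed that average are listed under Table 1 in section 2.14.1: "Postoperative pain at 6, 12, 24, 36, 48, and 72 hours after surgery will be recorded using the VAS pain scores". The abstract says only that the primary outcome is pain intensity on the VAS, which fits either an average or a single time point.

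Section 2.17 plans on one time point. Its pilot evidence begins "Our pilot study shows that VAS pain scores 72 hours after lumbar spinal fusion surgery were reported to be 2.1 ± 1.6" for the cocktail arm, set against 5.6 ± 1.7 without the injection. The planning assumption drawn from this is: "we hypothesized that VAS pain score 72 hours after surgery will be 2.5 for the cocktail group and 5.0 for the control group". The SD is taken as 2.5 and allocation is equal. The error rate is "alpha value = 0.05, 2-sided" and the power 80%. The result is 14 per group, raised to 18 per group (36 in total) for 20% dropout. No difference, SD or within-patient correlation is given for the 3-day average, and no sentence links the 72-hour figures to it.

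**The concern.** A 3-day average and a single 72-hour score are different variables. Averaging several correlated readings lowers the SD, which raises power. The treatment difference in the average may be smaller or larger than the difference at 72 hours, and that can move power a long way. A power figure computed for one variable cannot be carried over to the other without a stated link.

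There is a specific reason to doubt that the 72-hour difference can stand in for the average. Both arms have patient-controlled sufentanil until the pump is removed at 48 hours (sections 2.10 to 2.12). Five of the six readings fall within or at the end of that period, and only the 72-hour reading clearly follows it. If patients titrate themselves towards similar pain, the earlier differences could be narrower. This is an inference, since the article gives no pain scores before 72 hours.

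At stake is whether a 36-patient trial has the power it claims on the endpoint that decides it.

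**Working it through.** **1. The plan's own figure (72-hour score).** Inputs from section 2.17: difference 2.5, SD 2.5, two-sided alpha 0.05, power 80%, 1:1 allocation.

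- Normal approximation: n per group = 2 × (1.960 + 0.842)² × (2.5/2.5)² = 15.7, so 16.
- Exact t test (noncentral t): 17 per group (power 78.1% at 16, 80.7% at 17).
- Power at the stated 14 per group: 75.4% by normal approximation, 72.1% by t test.
- A one-sided t test at 14 per group gives 82.4%, but the plan states a two-sided test.
- Dropout step: 14/(1 − 0.20) = 17.5, so 18 per group. This step is correct. From 16 or 17 it would give 20 or 22 per group, 40 or 44 in total.

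So 14 per group does not deliver 80% even for the 72-hour score.

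**2. The declared endpoint (3-day average).** The article gives no inputs for it, so these are assumptions: six equally weighted readings, the same SD at each, and a common within-patient correlation ρ of 0.3 to 0.7.

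- SD of the mean of six = SD × √((1 + 5ρ)/6).
- With SD 2.5 (section 2.17): 2.5 × √(2.5/6) = 1.61 at ρ = 0.3, and 2.5 × √(4.5/6) = 2.17 at ρ = 0.7.
- With SD 1.7 (the larger pilot SD): 1.10 and 1.47.
- Average difference = (5x + 2.5)/6, where x is the difference at the five readings up to 48 hours and 2.5 is the difference at 72 hours. For x = 2.5, 1.5 and 1.0 this gives 2.50, 1.67 and 1.25. The values of x are illustrative.
- Power from the noncentral t distribution with 26 degrees of freedom and noncentrality (difference/SD of mean) × √(14/2).

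| Average difference | Power, SD 2.5 (ρ 0.3 to 0.7) | Power, SD 1.7 (ρ 0.3 to 0.7) |
|---|---|---|
| 2.50 | 98% to 84% | above 99% throughout |
| 1.67 | 75% to 50% | 97% to 82% |
| 1.25 | 50% to 31% | 83% to 58% |

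One line in full: difference 1.25, SD 2.5, ρ = 0.7 gives noncentrality (1.25/2.165) × √7 = 1.53 and power 31%.

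**3. Does the weighting matter?** Under trapezoidal time-weighting from 6 to 72 hours, the 72-hour reading has weight 12/66 = 18.2%. The two reduced scenarios then give 0.818 × 1.5 + 0.182 × 2.5 = 1.68 and 0.818 × 1.0 + 0.182 × 2.5 = 1.27, almost the same as equal weighting.

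**The case against.** The strongest reply is that the planning was cautious. The pilot difference of 5.6 − 2.1 = 3.5 was cut to 2.5, and the pilot SDs of 1.6 and 1.7 were raised to 2.5. Averaging lowers the SD further, so power for the average could exceed 80%. That stands: with a constant 2.5-point difference it does exceed 80% for ρ from 0.3 to 0.7. The low figures come from pairing an inflated SD with a reduced difference, which is why the results at SD 1.7 are shown beside them.

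The argument from patient-controlled analgesia is also open to challenge. Rescue tramadol is available after pump removal (section 2.13), so the 72-hour score is not free of opioid either. The injection is given at wound closure, so a larger early effect is equally possible. Section 2.21 plans a transformation to deal with the effect of analgesic consumption on pain scores. A reader might infer that the trial is underpowered for the average. The documents do not support this, because the direction is unknown.

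A reader might also infer two rival primary endpoints and an inflated type I error. The documents do not support that either: section 2.15 names one primary outcome, and section 2.17 uses the 72-hour score as a planning input without calling it an endpoint. The phrase "daily visual analog scale (VAS) pain score" in section 2.14.1 is only a summary, since the exact times follow it. How the readings are weighted may be left to an analysis plan.

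None of this supplies the missing link. The article states both the endpoint and the sizing variable, and they differ. An analysis plan could define the average, but it could not turn a 72-hour calculation into one for the average.

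**Conclusion.** The point holds in a limited form. The primary endpoint is the 3-day average, the sample size is calculated for the 72-hour score, and the 80% power is not shown for the endpoint that decides the trial. The size and direction of the discrepancy cannot be fixed from the article. At 14 per group, power for the average runs from about 98% to 31% at SD 2.5 over the three scenarios. The two reduced differences give 97% to 58% at SD 1.7. All of these rest on an assumed common SD, a correlation of 0.3 to 0.7 and illustrative differences before 72 hours.

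One part needs no such assumptions: on section 2.17's own inputs, 14 per group gives about 72% power by a two-sided t test for the 72-hour score.

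**What to change.** Use one endpoint in the abstract, section 2.15 and section 2.17. There are two ways:

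- **Keep the 3-day average.** State that it is a pre-specified summary of the 6 to 72 hour readings, since no reading is scheduled before 6 hours. Restate in section 2.17 the expected difference, the SD and the power for that average, from the pilot data if they contain the earlier readings, otherwise as declared assumptions with a range. Name the VAS at 72 hours as a secondary outcome.
- **If the pilot supports only the 72-hour score,** declare the VAS at 72 hours as primary in the abstract and section 2.15.

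In either case, correct the figure for the present inputs: report about 72% power at 14 per group for the 72-hour score, or 17 per group (22 after 20% dropout, 44 in total) if 80% by t test is to be kept.

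The restatement costs wording and a recalculation, with no new measurements. The downside is that the stated power may look less favourable. Restoring 80% for the 72-hour score would mean 44 − 36 = 8 more patients.

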### Secondary outcome measures

2.16

#### Sufentanil consumption

2.16.1

Sufentanil consumption of IV-PCA during the first 48 hours postoperatively will be recorded.

#### Time to first use of IV-PCA

2.16.2

The time to first use of IV-PCA and proportion of the patients during the first 48 hours postoperatively will be recorded.

#### Rescue analgesia consumption

2.16.3

The frequency and total dosage of the rescue analgesics (tramadol hydrochloride injection) during the first 72 hours postoperatively will be recorded.

#### Safety

2.16.4

The presence of side effects during the entire postoperative period will be recorded, including nausea, vomiting, and other adverse events and complications.

### Sample size

2.17

The sample size calculation was based on the following parameters:

(1)alpha value = 0.05, 2-sided;(2)power = 80%.

The minimal clinical significance in VAS pain score was defined as the mean difference between current and preceding scores when the subject reported “a little worse” or “a little better” pain. Our pilot study shows that VAS pain scores 72 hours after lumbar spinal fusion surgery were reported to be 2.1 ± 1.6 in patients receiving cocktail analgesic injection and 5.6 ± 1.7 in patients without. Based on these findings, we hypothesized that VAS pain score 72 hours after surgery will be 2.5 for the cocktail group and 5.0 for the control group, with a standard deviation set at 2.5 and a ratio of patients in the cocktail to the control group of 1:1. Calculations showed that a sample size of 14 patients per group to detect a difference in VAS pain score between the 2 groups after treatment. Assuming a 20% dropout rate, 18 patients per group, or a total of 36 patients, are required.

It is anticipated that recruitment for this study will take 6 months to complete, using 1 surgeon to reduce surgical variability. Data collection for each patient will occur during the first 72 hours postoperatively and at a routine 4-week follow-up appointment. No further follow up will be routinely arranged. Any patients requiring specific follow up will have this arranged on an individual basis.

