### Data analysis

2.21

Data distribution will be tested for normality using the Shapiro–Wilk test. Skewed data will be corrected by logit-transformation as appropriate and subsequently examined using parametric test in order to preserve statistical power. For data set that cannot be normalized by logit-transformation, nonparametric test will be applied. Group comparison will be done by Student *t* test and Mann–Whitney *U* test for parametric and nonparametric data, respectively. Pearson Chi-square will be used for categorical variables. In strata where the expected counts are less than 5, Fisher exact test will be used. Univariate logistic regression and simple linear regression will be performed to determine potential predictors associated with binary outcomes and continuous outcomes, respectively. For predictors significantly associated with the outcomes of interest (*P* < .1), they will be further examined for co-linearity using Chi-square test, 0-order Pearson product-moment correlation, or Student *t* test as appropriate. For continuous variables with variable inflation factor greater or equal to 10, only 1 variable will be kept for subsequent analysis. After removing redundant co-variates, multivariate regression models will be built. The goodness-of-fit of the final models will be determined by the Hosmer–Lemeshow test (logistic regression) or *R*^2^ (multiple linear regression), respectively. For time-to-event outcomes, multivariate Cox proportional hazard regression models will be built. The cumulative probability of an outcome event over time will be presented in form of Kaplan–Meier curves.

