To determine changes of analgesic consumption and pain score over time between groups, a generalized estimating equation population average regression will be used. To correct for ceiling effect of analgesic consumption on pain score reporting, an empirical logit transformation will be applied in before comparison between groups. For missing data less than 10%, imputation will be performed using median for continuous and ordinal variables. For nominal variables, the most common category will be imputed. If there are more than 10% missing data, multiple imputation will be used. Intention-to-treat and per-protocol analyses will be performed to account for possible missing data. *P*-value less than .05 will be considered as statistical significance. All statistical analyses will be 2-tailed and performed using Statistical Package for Social Sciences (SPSS version 24.0, Chicago, IL).

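### The stated 14 patients per group gives about 72% power under the plan's own inputs, not 80%, so 36 patients do not carry the stated power after the planned dropout

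*Protocol article*

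**What the plan says.** Section 2.17 (Sample size) of the protocol article gives every input to the calculation:

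- error rate: "alpha value = 0.05, 2-sided", with power of 80%;
- hypothesised means: "VAS pain score 72 hours after surgery will be 2.5 for the cocktail group and 5.0 for the control group";
- variability: "with a standard deviation set at 2.5";
- allocation: "a ratio of patients in the cocktail to the control group of 1:1".

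From these it reports "a sample size of 14 patients per group to detect a difference in VAS pain score between the 2 groups after treatment", and then: "Assuming a 20% dropout rate, 18 patients per group, or a total of 36 patients, are required".

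Section 2.21 (Data analysis) matches a two-sided t-test calculation. It says "Group comparison will be done by Student" *t* test, with Mann–Whitney *U* for data that cannot be normalised, and "All statistical analyses will be 2-tailed".

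**The concern.** The difference equals the SD, so the standardised difference is exactly 1.0. For that effect, a two-sided 5% test with 80% power needs 16 or 17 patients per group, depending on the formula. A figure of 14 is too low under either.

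This calculation is the only justification given for enrolling 36 patients. If it is wrong, readers and the ethics committee have been given a power figure that the design does not have at the evaluable number it plans for. A null result would then be read as coming from a trial with a 20% type II error when, under the plan's own assumptions, the error is nearer 28%.

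**Working it through.** **Inputs (section 2.17).** Difference Δ = 5.0 − 2.5 = 2.5; SD σ = 2.5; d = Δ/σ = 1.0; two-sided α = 0.05; power 0.80; 1:1 allocation; dropout 20%.

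**1. Trying to reproduce 14 per group.**

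Normal approximation: n = 2(z₀.₉₇₅ + z₀.₈₀)² / d² = 2(1.960 + 0.842)² / 1.0² = 15.7, so 16 per group.

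Two-sided t test (exact, noncentral t): n = 16.7, so 17 per group.

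Neither gives 14.

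**2. Power at the stated number.** The noncentrality parameter is d√(n/2). At n = 14 it is √7 = 2.646, on 26 degrees of freedom.

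- Normal approximation: Φ(2.646 − 1.960) = Φ(0.686) = 75.4%.
- t test: 72.1%.

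| Evaluable per group | Power, t test | Power, normal approximation |
|---|---|---|
| 14 | 72.1% | 75.4% |
| 15 | 75.3% | 78.2% |
| 16 | 78.1% | 80.7% |
| 17 | 80.7% | 83.0% |
| 18 | 83.0% | 85.1% |

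**3. The dropout step.** 14/0.8 = 17.5, rounded up to 18 per group and 36 in total. This step is correct. Applying the plan's own loss rate to it, 18 × 0.8 = 14.4 evaluable per group, which gives about 72–73% power by t test.

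From the corrected starting numbers:

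- t test: 17/0.8 = 21.25, so 22 per group, 44 in total;
- normal approximation: 16/0.8 = 20 per group, 40 in total.

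**4. What 14 per group does support.** With 80% power (two-sided t test) the detectable d is 1.100. That is 1.100 × 2.5 = 2.75 points at SD 2.5. For a 2.5-point difference, the SD would have to be 2.5/1.100 = 2.27.

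**5. Where 14 might come from.** The document does not say, so this is conjecture.

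- A one-sided 5% t test needs 13.1, so 14 per group (power 82.4%). That contradicts the two-sided alpha in 2.17 and the two-tailed rule in 2.21.
- A two-sided t test with an SD of 2.25 also gives 14 (power 81%), but the stated SD is 2.5.
- The pilot values (2.1 ± 1.6 against 5.6 ± 1.7) need only about 5 per group, so they are not the source.

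**The case against.** The arithmetic is hard to dispute; the case on the other side is that it matters less than it seems.

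- **The planning values are cautious.** The pilot difference was 3.5 points with SDs of 1.6 and 1.7. At 14 per group, a 2.5-point difference with SD 1.7 has 96% power, and a 3.5-point difference with SD 2.5 has 95%. This stands as a limit on the practical harm. It does not rescue the figure: the plan deliberately chose a difference of 2.5 and an SD of 2.5 and attached its 80% claim to them.

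- **The primary outcome in 2.15 is an average over three days, not the 72-hour score.** Suppose, beyond what the document says, that SD 2.5 applied at each of the six assessments and the difference averaged 2.5. Power for the mean at 14 per group would then be about 92%, 84% or 76% at within-patient correlations of 0.5, 0.7 or 0.9. So the shortfall is shown for the calculation as written, and the power for the averaged score is not established either way. The mismatch between the two outcomes is a separate matter.

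- **The dropout margin may absorb the error.** Follow-up for pain lasts only 72 hours, and 17 evaluable per group already gives 80.7%, so one loss per group is tolerable. That is a loss of about 5% (1/18), while the plan itself assumes 20%. The imputation planned in 2.21 does not close the gap, because filling in a median adds no information about the treatment difference.

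**Conclusion.** The concern holds. Under the inputs printed in section 2.17, 14 evaluable patients per group gives 72.1% power by the planned t test (75.4% by the normal approximation), not 80%. The required number is 17 per group (16 by the normal approximation). The choice of formula does not explain the gap, and nothing elsewhere in the article supplies an input that yields 14.

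The type II error of about 28% is conditional on a true 2.5-point difference at 72 hours, an SD of 2.5 and the planned 20% dropout. With smaller losses, a larger effect or a smaller SD, the power would be higher. The plan's 80% claim, however, is made under exactly these conditions.

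**What to change.** Correct the calculation in section 2.17 in one of two ways.

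1. **Keep 36 patients and restate the power.** Say that 14 evaluable per group gives about 72% power for a 2.5-point difference with SD 2.5 (two-sided t test, α = 0.05), rising to 83% with no dropout. Alternatively, say that the difference detectable with 80% power at 14 per group is 2.75 points.
2. **Keep the claim of 80% power at 2.5 points.** State 17 evaluable per group, 22 randomised per group and 44 in total.

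The first option is enough to put the document right. It costs one corrected paragraph and a less favourable power figure, with no extra patients and no change to randomisation, outcomes or analysis. The second adds 44 − 36 = 8 patients. Either way, the text should name the test and formula used, so that the number can be reproduced.

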### Timeline

2.18

This is a 6-month study commencing January 2018 and ending June 2019. See Table 1 and Figure 1 for time points and recruitment progress.

### Criteria for discontinuation

2.19

Every effort will be made to retain patients in the trial and to minimize withdrawals. However, the trial will be discontinued on condition that any SAEs happen. Additionally, patients may request to be withdrawn from this study at any time without any reason. Intention to treat and “as treated” analyses will be performed.

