### Perioperative management

2.12

Surgery will be performed under general anesthesia with standardized fashion. A standardized intraoperative strategy for fluid management will be applied which consists of 0.9% saline at 5 ml/kg/h and hydroxyethyl starch colloid at 7.5 ml/kg/h. At the end of the surgery, the PCA pump will be started on without a basal dosage, which will be removed 48 hours later. After surgery, patients will be taken to the recovery room and monitored according to standard hospital policy. Patients will be educated with the use of the PCA device and discharged to the ward, once recovery room discharge criteria have been met. Patients will receive supplemental oxygen via nasal cannula at 2 l/min for 24 hours. The time to first mobilization will be recorded and the patient will continue to be monitored until discharge. Any serious adverse events (SAEs) will prompt follow up. Patients will be followed up routinely at 4 weeks after discharge by the spine specialist. Symptoms of nerve damage will be actively sought at this consultation.

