### Adverse event reporting and safety

2.20

All adverse events will be recorded and discussed at weekly safety meetings by at least 2 investigators. If clinically indicated, the nature of the analgesia administered in the study may be revealed. After assessment by the Principle Investigator, any SAEs will be reported to the Ethics Committee in PUMCH. All SAEs will be also reported to the China Food and Drug Administration by the Ethics Committee.

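### As worded, the discontinuation rule ends the whole trial at the first serious adverse event; a patient-level rule was probably meant, but nothing in the article says so

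*Protocol article*

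**What the plan says.** Section 2.19 (Criteria for discontinuation) has four statements, in this order:

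1. On retention: "Every effort will be made to retain patients in the trial and to minimize withdrawals".
2. On SAEs: "the trial will be discontinued on condition that any SAEs happen".
3. On withdrawal: "patients may request to be withdrawn from this study at any time without any reason".
4. On analysis: "Intention to treat and “as treated” analyses will be performed".

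SAEs are handled in two other places. Perioperative management (2.12) says "Any serious adverse events (SAEs) will prompt follow up". Adverse event reporting and safety (2.20) provides for weekly discussion of adverse events by at least two investigators and for unblinding: "If clinically indicated, the nature of the analgesia administered in the study may be revealed". It then sets out reporting: "After assessment by the Principle Investigator, any SAEs will be reported to the Ethics Committee in PUMCH", and "All SAEs will be also reported to the China Food and Drug Administration by the Ethics Committee".

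**The concern.** The SAE sentence makes the trial its subject and puts no limit on the trigger: not relatedness to the injection, arm, number of events or any review. Read as written, one postoperative SAE with no link to the study injection, even in a saline patient, ends the study, possibly well before 36 patients are enrolled.

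If the authors meant that the affected patient is discontinued, the sentence does not say so, and a team that sensibly carries on after an SAE is at odds with the rule it published.

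The patient-level reading does not work cleanly either. The injection is given once, before wound closure (2.10), so it cannot be stopped after a postoperative SAE. What is left to discontinue is the patient-controlled analgesia (PCA), which runs to 48 hours, and outcome follow-up. Ending follow-up would cut against the retention aim and the intention-to-treat analysis in the same section.

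This is a stated rule that is worded wrongly. It is not a complaint that operational detail is missing from a condensed article.

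**Working it through.** **Reading the text.** Four points favour a patient-level meaning:
- The sentence stands between one on retaining patients and one on patients' withdrawal.
- Intention-to-treat and as-treated analyses follow it.
- Section 2.20 speaks of SAEs in the plural and of a continuing weekly review.
- Sections 2.12 and 2.17 arrange individual follow-up.

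Against this, section 2.19 uses patients as the subject when it means patients, and uses the trial here. Sections 2.12, 2.17 and 2.20 do not restate the rule at patient level, limit it, or say that the trial continues after an SAE.

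**What the literal rule would do.** The plan gives no figure for this rule, so there is none to reproduce.

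Inputs:
- Planned total N = 36, with 14 evaluable per group, so 28 (Sample size, 2.17).
- Recruitment over 6 months (2.17); routine visit 4 weeks after discharge (2.12).
- SAE risk per patient p = 1%, 2%, 5%. These are assumptions, as is independence between patients.
- L = number of further patients enrolled before an SAE becomes known. L = 0 means it is known at once. For an SAE known only at the 4-week visit, 36 patients over about 26 weeks is 1.38 per week, or 5.5 in 4 weeks. This is rounded up to L = 6 because the visit is counted from discharge and length of stay is not stated.

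Formulas:
- At least one SAE among all 36: 1 − (1 − p)^36
- Enrolment cut short: 1 − (1 − p)^(35 − L)
- Mean enrolment: L + the sum of (1 − p)^k for k = 0 to 35 − L

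Worked for p = 2%: 1 − 0.98^36 = 1 − 0.483 = 0.517. With L = 0, 1 − 0.98^35 = 1 − 0.493 = 0.507. With L = 6, 1 − 0.98^29 = 1 − 0.557 = 0.443.

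| Assumed SAE risk per patient | At least one SAE in 36 | Cut short, L = 0 | Cut short, L = 6 | Mean enrolment, L = 0 | Mean enrolment, L = 6 |
|---|---|---|---|---|---|
| 1% | 30.4% | 29.7% | 25.3% | 30.4 | 32.0 |
| 2% | 51.7% | 50.7% | 44.3% | 25.8 | 28.7 |
| 5% | 84.2% | 83.4% | 77.4% | 16.8 | 21.7 |

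The Timeline (2.18) dates, January 2018 to June 2019, span about 18 months. At that pace about 2 patients enrol in 4 weeks, and L = 2 gives 28%, 49% and 82%, inside the ranges above.

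**What the patient-level rule would do.** Expected number discontinued = 36p = 0.36, 0.72 and 1.8. The dropout allowance is 36 − 2 × 14 = 8 patients. The trial does not stop.

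**The case against.** The strongest reply is that the context settles the meaning. The SAE sentence is introduced as an exception to retaining patients, and patient-requested withdrawal is added as a second exception of the same kind. On that view the trial is loose English for participation in the trial. Weekly safety meetings, unblinding when clinically indicated and onward reporting of all SAEs would be odd provisions in a study that ends at the first event. The probabilities then describe a reading probably not intended, and their spread (25% to 84%) mostly reflects the assumed rates.

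Much of this stands. The patient-level meaning is the more likely one, and the stop probabilities illustrate the literal rule; they are not evidence that this trial is at risk. The 6-patient lag is an upper case, since inpatient monitoring and weekly review would usually bring SAEs to light sooner. The charge that a continuing team breaks its own rule also has force only if the literal words are taken as the rule.

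It does not clear the text. An unqualified stopping rule that says something other than what was probably meant is still stated wrongly, and no other section overrides it. That a full protocol may exist excuses omissions, but not a rule the article states explicitly. Nor does the patient-level reading make the sentence sound, because the single injection cannot be withdrawn afterwards and ending follow-up would undercut the intention-to-treat analysis.

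**Conclusion.** The concern holds, as a cheap improvement and no more. The words set a trial-level stop at the first SAE of any cause, and nothing in the article corrects them. Confidence is medium because the intended meaning is probably patient-level.

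Taken literally, the rule would leave the trial with roughly a one-in-four to five-in-six chance of closing early, over assumed SAE risks of 1% to 5% per patient. At 5%, mean enrolment would be 17 to 22, below the 28 evaluable patients that section 2.17 requires. Taken at patient level, the loss is at most about 2 expected patients against an allowance of 8, and the planned size is not threatened. Under neither reading does the wording bias the treatment estimate or alter the type I error of a completed trial.

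**What to change.** Replace the SAE sentence in section 2.19. The new text should say that:
- an SAE triggers follow-up, investigator assessment and Ethics Committee reporting, as sections 2.12 and 2.20 already provide;
- the affected patient is managed as clinically indicated, including unblinding or stopping PCA;
- the patient stays in outcome follow-up for the intention-to-treat analysis.

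If a trial-level stop is wanted, give it its own sentence and make it follow Ethics Committee review of SAEs judged related to the injection. This second part is optional; correcting what is discontinued, and on what trigger, is what removes the defect.

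The cost is a one-sentence amendment with ethics notification. The one small downside is that a first SAE would lead to review and not to automatic termination.
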